### Data Analysis

The primary analysis is the change in systolic blood pressure (SBP) from baseline to 12 months. Meta-analyses have found that for a given blood pressure, SBP predicted over 90% of the risk of ischemic heart disease and stroke and that a 2 mm Hg decrease in SBP could reduce stroke and ischemic heart disease mortality [46]. Analysis will fit a linear regression model with the outcome of 12-month SBP, including baseline SBP and a binary predictor of Unite care model patient (yes vs no) as independent variables.

Other secondary analysis end points will include determining whether functional and cognitive limitations are associated with care model usage, change in physical and social environment, and moves out of the Unite clinic building. To determine if functional and cognitive limitations, including activity limitations and AD/ADRD are associated with Unite care model usage, the research team will build a logistic regression model predicting Unite utilization, including age, sex, race, ethnicity, AD/ADRD status, level of functional disability, self-reported health, and baseline hypertension as independent variables. Change in physical and social environment (item counts) will be assessed using a Poisson regression with an outcome of 12-month values, adjusting for baseline values and including an intervention indicator. Moves out of the clinic building will be assessed by comparing moves out of the building in the 2 years prior to the Unite care model compared to year 2 of the Unite care model.

Of the 300 older adults residing in the Unite building, we estimate that 5% will elect not to enroll, resulting in a study population of 285 older adults. We estimate that we will have 89% power to detect a 2-point change in SBP within older adults assuming a mean baseline SBP of 162 mm Hg and SE of change in SBP over time of 10 mm Hg, based on prior data in this community and community studies [47,48], and a 10% loss to follow-up using an analogous test to our primary analysis. If loss to follow-up increases to 20%, power to detect a 2-point change in SBP would decrease to 85%. The effect may be larger. We will have 100% power to detect a 4-point SBP change if loss to follow-up were 20%.

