## Discussion

### Anticipated Findings

We anticipate the following outcomes: (1) among older adults residing in the Unite clinic building, those with functional and cognitive limitations (ie, activity limitations, AD/ADRD) will be more likely to use the Unite care model than those without limitations; (2) among older adults residing in the Unite clinic building, those who receive care through the Unite care model will have reduced SBP compared to those who do not receive care through the Unite care model; and (3) Among older adults residing in the Unite clinic building, those who receive care through the Unite care model will have an increase in physical environment modifications and a decrease in social isolation compared to those who do not receive care through the care model.

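### The stated 89%, 85% and 100% powers belong to a one-group test of mean change; the primary user/non-user regression coefficient has far less power at the planned sample size

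*Protocol article*

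**What the plan says.** In the protocol article, the Data Analysis section under Aim 2 first names the primary analysis as the change in SBP between baseline and 12 months. It then specifies the model: a linear regression of 12-month SBP "including baseline SBP and a binary predictor of Unite care model patient (yes vs no) as independent variables". Anticipated Findings words the hypothesis as the same contrast: "those who receive care through the Unite care model will have reduced SBP compared to those who do not receive care".

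The power statement closes the Data Analysis section. It starts from 300 residents less 5% who decline, "resulting in a study population of 285 older adults". It gives "89% power to detect a 2-point change in SBP within older adults assuming a mean baseline SBP of 162 mm Hg" and an "SE of change in SBP over time of 10 mm Hg", with "a 10% loss to follow-up using an analogous test to our primary analysis". Power is put at 85% for 2 mm Hg if loss rises to 20%, and at 100% for 4 mm Hg with that loss. No user share, between-group difference, significance level or baseline/12-month correlation is given.

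The Results section reports 179 residents enrolled and 131 with 12-month outcomes, and says the Aim 2 analysis had yet to begin.

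**The concern.** The power statement describes one group changing over time. The primary model estimates a difference between two groups inside that cohort. A single mean uses all completers against a fixed value of zero, whereas a user/non-user coefficient splits the same completers in two and is estimated less precisely. If the printed powers belong to the first test, they say little about the second, and the claim that the tests are analogous is wrong.

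This matters for how the primary result is read. The article presents 2 mm Hg as a reduction that could lower stroke and heart disease mortality. A reader who believes the study had 89% power for that difference may give a non-significant coefficient more weight than it can bear.

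**Working it through.** **Inputs from the Data Analysis section.** Enrolled N = 300 × 0.95 = 285. Completers: 285 × 0.90 = 256.5 (256 used below) and 285 × 0.80 = 228. Effects: 2 and 4 mm Hg. Variability of change: 10 mm Hg. From Results: 131 residents with 12-month outcomes.

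**Assumptions, not in the document.** Two-sided 5%; user share p from 20% to 50%; baseline/12-month correlation ρ where used. The printed SE of 10 is read as the SD of individual change. Taken literally as a standard error, a 2 mm Hg effect would be 0.2 standard errors, with power near 5%, so the printed figures require the SD reading.

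**Step 1: reproduce the printed powers.** One-sample test of mean change, SE = 10/√n, noncentral t:

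| Case | SE | Effect/SE | Power | Printed |
|---|---|---|---|---|
| n = 256, 2 mm Hg | 0.625 | 3.20 | 89.0% | 89% |
| n = 228, 2 mm Hg | 0.662 | 3.02 | 85.2% | 85% |
| n = 228, 4 mm Hg | 0.662 | 6.04 | >99.9% | 100% |

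All three match. One-sided 5% would give about 94% and 91% for the first two rows, so the two-sided assumption is supported by the article's own figures.

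**Step 2: power for the user/non-user coefficient.** SE = 10/√(n·p·(1−p)), noncentral t with n−3 df. For example, n = 256 and p = 0.5 give SE = 10/√64 = 1.25, so 2/1.25 = 1.6.

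| User share | n = 256, 2 mm Hg | n = 228, 2 mm Hg | n = 228, 4 mm Hg |
|---|---|---|---|
| 50% | 35.7% | 32.4% | 85.2% |
| 30% | 30.9% | 28.1% | 78.7% |
| 20% | 24.7% | 22.5% | 67.2% |

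An equal split is the most favourable, so at SD 10 no user share brings power for 2 mm Hg above 36%.

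**Step 3: credit for baseline adjustment.** With equal SDs at both visits, the variance of change is 2σ²(1−ρ) = 100 and the residual variance after adjustment is σ²(1−ρ²) = 100(1+ρ)/2.

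- ρ = 0.5: residual SD = √75 = 8.66. Power for 2 mm Hg is 31-45% at n = 256 and 28-41% at n = 228.
- ρ = 0 (extreme): residual SD = √50 = 7.07. Power at n = 256 with an equal split is 62%.

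Reaching 89% with an equal split would need a residual SD of about 5.0 mm Hg.

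**Step 4: difference detectable with 89% power.** (1.960 + 1.227) × SE = 3.186 × SE, at SD 10:

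| User share | n = 256 (planned) | n = 131 (12-month outcomes) |
|---|---|---|
| 50% | 4.0 mm Hg | 5.6 mm Hg |
| 30% | 4.3 mm Hg | 6.1 mm Hg |
| 20% | 5.0 mm Hg | 7.0 mm Hg |

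**The case against.** The best defence is that the Data Analysis section introduces the primary analysis as a change from baseline to 12 months, and the Abstract describes risk factor reduction in the same way. On that wording, a one-group power calculation is consistent with the label. The ambiguity is real and should be resolved. It does not rescue the figures: the only model specified contains the user indicator, and Anticipated Findings states the user/non-user hypothesis. If a building-wide change was meant, the label and the model conflict, and one of them has to change.

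A second objection is that user share, correlation and significance level are all assumed. That is so, and the exact power depends on them. The conclusion does not, since the most favourable combination examined gives 62%.

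A reader might also infer more than the article supports:

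- **That the two-group variance is always at least four times larger.** This holds only without the gain from baseline adjustment. For the stated model with an equal split the ratio is 4(1+ρ)/2, which is 3 at ρ = 0.5.
- **That 45% follows from the article's own inputs.** It needs the assumed correlation of 0.5, equal SDs and an equal split. The printed N, effect and SD alone cap power at 36%.
- **That this study can detect 4-5 mm Hg.** That is a planned-N figure; with 131 completers the range is higher.
- **That a null coefficient would decide the programme's future.** No such rule is given. The Overall Assessment section describes a holistic judgement by an advisory board in which no single metric is expected to suffice.
- **That the sum was done wrongly.** The arithmetic reproduces. It was done for a different test.

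**Conclusion.** The point holds. The printed powers describe a one-group test of mean change, which is not analogous to the primary regression. For the Unite coefficient at the planned N and SD 10, power for 2 mm Hg is about 25-36% with 10% loss and 22-32% with 20% loss, against 89% and 85% printed. For 4 mm Hg with 20% loss it is about 67-85%, against 100%. Baseline adjustment raises the 2 mm Hg figure to at most 45% at a correlation of 0.5, and to 62% at zero correlation.

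These figures rest on a two-sided 5% test, a user share of 20-50% and the SD reading of the printed SE. Data collection has ended, so the correction bears on how the primary result is reported and interpreted, not on recruitment.

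**What to change.** 1. Reconcile the change-from-baseline label with the regression, so that the primary estimand is stated once as the baseline-adjusted user/non-user difference in 12-month SBP.
2. Delete "using an analogous test to our primary analysis" and the 89%, 85% and 100% figures. Replace them with power or detectable difference for the Unite coefficient over a stated range of user shares and baseline/12-month correlations.
3. Label the planned-N result as such (about 4.0-5.0 mm Hg detectable with 89% power at 256 completers, SD 10). Beside it, give the figure for the 131 residents with 12-month outcomes (about 5.6-7.0 mm Hg).
4. Interpret the primary coefficient by its confidence interval. Report any building-wide mean change as a separate, uncontrolled estimate.

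This costs wording only, with no added data or participants. The one downside is a less favourable stated power.

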### Overall Assessment of Unite Care Model

After executing these aims, true to our community-engaged approach, our advisory board comprised of older adults, Unite partners (housing and health care), insurance, and local government stakeholders will review the results. Our evaluation of the care model will be holistic and require considerable judgment as no single metric nor combination of metrics is likely to capture the complexities of the initial Unite experience. The panel will then judge whether the Unite care model is sufficiently promising to justify efforts to develop similar models of care.

## Results

This study was funded by the National Institutes of Health-National Institutes on Aging in April 2021 and received institutional review board approval from the University of Michigan in May 2021. Semistructured interviews for aim 1 began in July 2021 and are anticipated to end in April 2023, with an anticipated total 45 stakeholders, including administrators, providers, and older adult residents. Structured interviews for aim 2 began in June 2021 and ended in November 2022. For aim 2, at baseline, 265 residents were approached, of which 179 residents enrolled. In total, 149 residents completed 6-month outcomes and 131 residents completed the final 12-month outcome. Data analysis for aim 1 is anticipated to begin in summer 2023; analysis for aim 2 will begin in spring 2023.

## Discussion

### Anticipated Findings

We anticipate the following outcomes: (1) among older adults residing in the Unite clinic building, those with functional and cognitive limitations (ie, activity limitations, AD/ADRD) will be more likely to use the Unite care model than those without limitations; (2) among older adults residing in the Unite clinic building, those who receive care through the Unite care model will have reduced SBP compared to those who do not receive care through the Unite care model; and (3) Among older adults residing in the Unite clinic building, those who receive care through the Unite care model will have an increase in physical environment modifications and a decrease in social isolation compared to those who do not receive care through the care model.

### Strengths and Limitations

The evaluation of the Unite care model is at the intersection of community engagement and implementation science. The Unite care model is a community-led and community-implemented intervention where the academic partners are supporting the initiative by conducting the analysis. Cross-sector collaborations such as Unite where housing and health care are partnering is 1 approach to addressing adverse social determinants of health. Often, investment in 1 sector accrues benefits in another sector while increasing the costs and resource usage in the investing sector [49-51]. In this case, the Unite care model is initiated and led by both housing and health care stakeholders, a cross-sector partnership promoting a shared assessment of value [52]. Multilevel interventions, such as the Unite care model, may interact to create synergistic effects, but rigorous assessments are rarely completed [53,54]. Our robust, holistic assessment of the Unite care model will inform whether larger scale testing of this new care model is warranted.

Potential challenges include recruitment and retention of participants in aim 2. We will employ our long-standing community recruitment and retention practices to reduce this barrier. Another potential pitfall lies in the study duration. The 2-year study timeframe may not be long enough to accrue outcomes of interest including aging in place and change in physical and cognitive impairment. Long-term follow-up of the Unite population could occur in subsequent research.

### Conclusions

Understanding the impact of combining older adult housing and health care will inform future cross-sector collaborations. Additionally, overlaying an implementation science-centered evaluation on a community-led initiative is an example of how academic teams can fully support their community partners.

## Abbreviations

AD: Alzheimer disease
ADRD: Alzheimer disease–related dementia
CAPABLE: Community aging in place-advancing better living for elders
SBP: systolic blood pressure
